### 7.2 Summary Treatment Schedule

Patients randomised to receive cediranib and gefitinib will receive their drugs according to the following schedule:

| Week                      | 1 |   |   |   |   |   |   | 2 |   |   |   |   |   |   | 3 |   |   |   |   |   |   |
|---------------------------|---|---|---|---|---|---|---|---|---|---|---|---|---|---|---|---|---|---|---|---|---|
| Cediranib 30mg od orally  | • | • | • | • | • | • | • | • | • | • | • | • | • | • | • | • | • | • | • | • | • |
| Gefitinib 500mg od orally | • | • | • | • | • | • | • | • | • | • | • | • | • | • | • | • | • | • | • | • | • |
| Week                      | 4 |   |   |   |   |   |   | 5 |   |   |   |   |   |   | 6 |   |   |   |   |   |   |
| Cediranib 30mg od orally  | • | • | • | • | • | • | • | • | • | • | • | • | • | • | • | • | • | • | • | • | • |
| Gefitinib 500mg od orally | • | • | • | • | • | • | • | • | • | • | • | • | • | • | • | • | • | • | • | • | • |

Patients randomised to receive cediranib and placebo will receive their drugs according to the following schedule:

| Week                     | 1               | 2               | 3               |
|--------------------------|-----------------|-----------------|-----------------|
| Cediranib 30mg od orally | • • • • • • • • | • • • • • • • • | • • • • • • • • |
| Placebo 500mg od orally  | • • • • • • • • | • • • • • • • • | • • • • • • • • |
| Week                     | 4               | 5               | 6               |
| Cediranib 30mg od orally | • • • • • • • • | • • • • • • • • | • • • • • • • • |
| Placebo 500mg od orally  | • • • • • • • • | • • • • • • • • | • • • • • • • • |

For both arms, each cycle will last 6 weeks and treatment will continue until progression as defined in 2.6.1.1, patient decision or the development of unacceptable toxicity (if there is progression treatment can continue if the investigator has the opinion that the patient is receiving benefit). There is therefore not a set number of treatment cycles.

At the beginning of each treatment cycle, all patients will be dispensed enough drug for one cycle (6 weeks) plus an extra weeks worth of tablets in case of delayed cycle start assessments. This is to prevent unnecessary treatment delays. Unused tablets must be returned to the pharmacy for accountability and destruction.

### 7.3 Trial Treatment Details

|                               |                                                                                                                                                                                                                                                                                                                                                                                                                                                            |
|-------------------------------|------------------------------------------------------------------------------------------------------------------------------------------------------------------------------------------------------------------------------------------------------------------------------------------------------------------------------------------------------------------------------------------------------------------------------------------------------------|
| Name of IMP            | Cediranib                                                                                                                                                                                                                                                                                                                                                                                                                                                  |
| Status of drug         | Unlicensed                                                                                                                                                                                                                                                                                                                                                                                                                                                 |
| Supplied by            | AstraZeneca                                                                                                                                                                                                                                                                                                                                                                                                                                                |
| Pharmaceutical form    | 35 x film-coated tablets per bottle, containing 30mg cediranib/tablet (20mg and 15mg tablets also available where dose reductions are necessary, see section 7.3.4 ). Other ingredients are mannitol, dibasic calcium phosphate anhydrous, sodium starch glycolate and magnesium stearate with a film coat containing hypromellose 2910, polyethylene glycol 400, red iron oxide, yellow iron oxide, black iron oxide and titanium dioxide |
| Dose and scheduling    | 30mg once daily* (1 tablet)                                                                                                                                                                                                                                                                                                                                                                                                                                |
| Mode of administration | Orally (in the morning at least one hour before food. If a meal is taken before the drug at least two hours should elapse before taking cediranib)                                                                                                                                                                                                                                                                                                         |
| Storage                | Less than 30°C. Protect from light, protect from moisture.                                                                                                                                                                                                                                                                                                                                                                                                 |

|                               |                                                                                                                                                                                                                                                                                                                                                                       |
|-------------------------------|-----------------------------------------------------------------------------------------------------------------------------------------------------------------------------------------------------------------------------------------------------------------------------------------------------------------------------------------------------------------------|
| Name of IMP            | Gefitinib (Iressa)                                                                                                                                                                                                                                                                                                                                                    |
| Status of drug         | Licensed for treating Non Small Cell Lung Cancer. Not licensed for treatment indication (Glioblastoma).                                                                                                                                                                                                                                                               |
| Supplied by            | AstraZeneca                                                                                                                                                                                                                                                                                                                                                           |
| Pharmaceutical form    | 100 x film-coated tablets per bottle, containing 250mg of gefitinib/tablet. Other ingredients are lactose monohydrate, microcrystalline cellulose (E460), croscarmellose sodium, povidone (K29-32) (E1201), sodium laurilsulfate, magnesium stearate, hypromellose (E464), macrogol 300, titanium dioxide (E171), yellow iron oxide (E172) and red iron oxide (E172). |
| Dose and scheduling    | 500mg once daily* (2 tablets)                                                                                                                                                                                                                                                                                                                                         |
| Mode of administration | Orally (may be taken with or without food)                                                                                                                                                                                                                                                                                                                            |
| Storage                | Less than 30°C                                                                                                                                                                                                                                                                                                                                                        |

|                               |                                                                                                                                                                                                                                                                                                                                        |
|-------------------------------|----------------------------------------------------------------------------------------------------------------------------------------------------------------------------------------------------------------------------------------------------------------------------------------------------------------------------------------|
| Name of IMP            | Placebo to match Gefitinib                                                                                                                                                                                                                                                                                                             |
| Status of drug         | Unlicensed                                                                                                                                                                                                                                                                                                                             |
| Supplied by            | AstraZeneca                                                                                                                                                                                                                                                                                                                            |
| Pharmaceutical form    | 100 x 250mg film-coated tablets identical to Gefitinib per bottle. The tablets contain lactose monohydrate, microcrystalline cellulose, croscarmellose sodium, povidone, sodium lauryl sulphate and magnesium stearate with a film coat containing hypromellose, macrogol 300, red iron oxide, yellow iron oxide and titanium dioxide. |
| Dose and scheduling    | 500mg once daily* (2 tablets)                                                                                                                                                                                                                                                                                                          |
| Mode of administration | Orally (may be taken with or without food)                                                                                                                                                                                                                                                                                             |
| Storage                | Less than 30°C                                                                                                                                                                                                                                                                                                                         |

\*unless dose reduction required, see [section 7.3.4](#).

**Cediranib and gefitinib/matching placebo should be taken at approximately the same time each day**, except on days they have a study visit, at which time patients should not take their study medication until after their assessments.

Cediranib, gefitinib and placebo will be packaged in high-density polyethylene (HDPE) bottles fitted with child resistant caps and tamper evident induction seals.

### 7.3.1 Treatment compliance

Patients should be given clear instructions on how and when to take their study drugs. The investigator or pharmacy must retain records of all study drugs administered. The UCL CTC will check these records to confirm compliance with the protocol administration schedule.

Patients should be encouraged to record when they take their study drugs each day in patient diaries.

Any dose reductions will be documented on the CRFs, along with reasons for the dose reduction. If a patient forgets to take a tablet, and it is within 6 hours of the scheduled time, then the patient should be advised to take the tablet as soon as possible. If it is more than 6 hours after the scheduled time, then study medication should not be taken for that day. Study medication should continue as previously scheduled on the subsequent day. A patient should not take more than a single day's dose of tablets within a day. Use of study medication in doses in excess of that specified in the protocol is considered to be an overdose. Refer to [section 10.2.1.1](#) for procedures in case of an overdose.

If the patient vomits within 30 minutes from taking the tablet or if they can identify the tablet in the vomit content, the patient can take a new tablet from the bottle. Trial medication should continue as usual on the subsequent day.

#### 7.3.1.1 Difficulties swallowing tablets

Entry into the DORIC trial requires that a patient is able to swallow tablets whole. However, for patients who are unable to swallow tablets due to their underlying disease or who become unable to swallow the tablet whole whilst on study, and who are considered to be benefiting from therapy, tablets may be administered by alternative methods as outlined below.

#### Cediranib

From the Cediranib IB (dated 08.11.2010).

Cediranib film-coated tablets have not been deliberately formulated to be dispersible tablets. However they may be administered as a dispersion in water (ie, either drinking water, sterile water [for

injection] or purified water). Liquids other than water should not be used, and the tablets should not be crushed or ground. Care should be taken to ensure that the whole dose is administered.

The following procedure is recommended:

Cediranib tablets may be dispersed in half a glass (2 fluid ounces or 50 ml) of non-carbonated drinking water. No other liquids should be used. The tablet is dropped in water, without crushing, stirred until dispersed (approximately 10 minutes) and the resultant dispersion swallowed immediately. Any residues in the glass are mixed with half a glass of water and swallowed. The liquid can also be administered through nasogastric or gastrostomy tubes.

Where patients require the dose to be administered by nasogastric or gastrostomy tubes, cediranib tablet(s) dispersed in water can be dosed with:

- Polyurethane (PUR) or Poly vinylchloride (PVC) naso-gastric, naso-intestinal or percutaneous endoscopic gastrostomy (PEG) feeding systems in conjunction with PUR syringes.
- PVC syringes are not recommended for use.
- Two system washes are conducted through the giving set to ensure the correct dose is obtained.

## **Gefitinib**

From the Iressa SmPC (dated 16.07.2009).

The tablet can be swallowed whole with some water or if dosing of whole tablets is not possible, tablets may be administered as a dispersion in water (non carbonated). No other liquids should be used. Without crushing it, the tablet should be dropped in half a glass of drinking water. The glass should be swirled occasionally, until the tablet is dispersed (this may take up to 20 minutes). The dispersion should be drunk immediately after dispersion is complete (i.e. within 60 minutes). The glass should be rinsed with half a glass of water, which should also be drunk. The dispersion can also be administered through a naso gastric or gastrostomy tube.

### **7.3.2 Pharmacy responsibilities:**

#### **Labelling**

The clinical study drugs (cediranib and gefitinib and gefitinib placebo) will be supplied by AstraZeneca Investigational Products and shipped by Fisher. Cediranib and gefitinib and gefitinib placebo will be

packed into white high-density polyethylene bottles with child resistant, tamper evident closures. Each container of cediranib, gefitinib or placebo will have an investigational use label permanently affixed to the outside and will be labelled in accordance with local regulations, stating that the drug is for investigational use only and should be kept out of reach of children. Instructions stating that the tablets should be taken at the same time each day will be included.

It is the investigator's responsibility to ensure the patient receives the correct dose.

All products distributed through the Interactive Web Response System (IWRS) system will be labelled with a unique medication ID number to allow drug tracking.

## **Storage**

All investigational products must be kept in a secure place under appropriate storage conditions. A description of the appropriate storage and shipment conditions are specified on the investigational product bottle label and in the Investigator's Brochure for cediranib (AZD2171, 2010) and SmPC for gefitinib. The investigator will instruct the patient about storage requirements for study medication. In the event of deviations from acceptable storage temperatures during the storage of trial drug at the site, the temperature excursions procedure should be followed (details will be held in the pharmacy file).

## **Accountability**

It is the investigator/institution's responsibility to establish a system for handling study treatments, including investigational medicinal products, so as to ensure that:

- Deliveries of such products from Fisher are correctly received by a responsible person.
- Such deliveries are recorded.
- Study treatments are handled and stored safely and properly.
- Study treatments are only dispensed to study patients in accordance with the protocol.
- Any unused products are accounted for and returned for destruction, or destroyed locally, in liaison with UCL CTC
- The study personnel will account for all drugs dispensed.
- Certificates of delivery, destruction and return must be signed

Destruction of these drugs will be conducted according to a site's local policy, at the request of AstraZeneca and/or the UCL CTC. Drug destruction logs must be maintained and returned to the UCL CTC as requested.

### **7.3.3 Drug accountability**

Accountability for cediranib, gefitinib and placebo at participating sites is the responsibility of the Principal Investigator, who may delegate this responsibility to the local pharmacist, or other appropriately qualified personnel. The responsible person will ensure that the cediranib, gefitinib and placebo are used only in accordance with this protocol and that appropriate records are maintained.

The site pharmacy must maintain accountability records for each drug including receipt, dispensing, return and destruction of medication. Accountability logs will be provided for each site pharmacy and accountability will be carried out throughout the trial whilst patients receive study medication. Drug delivery receipts, certificates of destruction of unused/expired medication and records of returned unused/expired medication must be kept in the pharmacy file. Temperature logs should be kept in the pharmacy file or centrally.

Patients should return any unused medication at their next visit to the pharmacy (e.g when collecting their next batch of trial medication). Returns should be counted by the pharmacist and recorded on accountability logs in the trial pharmacy site files. Patients who withdraw from the trial should arrange for medication to be returned to the pharmacy for accountability and destruction in cytotoxic waste according to local procedures.

Cediranib, gefitinib and placebo are supplied for DORIC patients only and must not be used outside the context of this protocol. Under no circumstances should the P.I. or other site personnel supply cediranib, gefitinib or placebo to other investigators, patients, or clinics, or allow supplies to be used other than directed by this protocol without prior authorisation from the supplier and notification to the Sponsor.

### **7.3.4 Dose modifications**

If cediranib or gefitinib is not tolerated, patients will be managed by allowing a dose reduction by one or more levels according to Table 5.

**Table 5**      *Dose reduction levels for cediranib and gefitinib*

| Dose Reduction level | Cediranib | Dose Reduction level | Gefitinib / placebo |
|----------------------|-----------|----------------------|---------------------|
| 0                    | 30mg/od   | 0                    | 500mg/od            |
| -1                   | 20mg/od   | -1                   | 250mg/od            |
| -2                   | 15mg/od   | -2                   | Stop drug           |
| -3                   | Stop drug |                      |                     |

The dose reduction schedule for specific toxicities are described in [Section 7.4.1](#) (Cediranib-related), [Section 7.4.2](#) (Iressa-related) and [Section 7.4.3](#) (related to both agents).

## 7.4 Management of general toxicity

The following general guidance is recommended for management of toxicities and dose de-escalation.

- All dose changes should be documented with clear reasoning and documentation of the approach taken
- Treat each of the toxicities with maximum supportive care (including withholding the experimental therapy where required)
- If the symptoms promptly resolve with supportive care, consideration should be given to continuing the same dose of study medications along with appropriate continuing supportive care, providing that continued treatment with study therapy is considered medically appropriate, in the opinion of the investigator as the patient is considered to be receiving benefit. If medically appropriate, dose reductions are permitted for study medications

Prophylactic antiemetics need only be given as required.

### 7.4.1 Management of toxicity attributable to cediranib

Dose interruptions should be used as the first approach to managing toxicity and dose reduction may be considered.

The events for which de-escalation of the cediranib dose is recommended include, with the EXCEPTION of hypertension:

- CTCAE grade 3 or higher toxicities of duration >3 days that are considered to be related to study treatment that are not responding to maximal supportive care within 48 hours, at the discretion of the investigator.

With the EXCEPTION of

- proteinuria (see [Section 7.4.1.1](#)),
- hypothyroidism (see [Section 7.4.1.2](#))
- hypertension (see [Section 7.4.1.4](#)), and
- reversible posterior leucoencephalopathy syndrome (RPLS) (see [Section 7.4.1.7](#)),

the following management plan should be followed for management of toxicity attributable to cediranib:

Dose interruptions should be used as the first approach to managing toxicity. For CTC Grade 3 or more, dosing with cediranib should be interrupted. Cediranib dosing may be withheld for up to 14 days (21 days in consultation with the CI) for management of toxicity. If a longer interruption is required due to unresolved toxicity, cediranib should be discontinued.

- If the symptoms promptly resolve to grade 1 or below with supportive care, consideration should be given to continuing the same dose of cediranib along with appropriate continuing supportive care
- If the symptoms of the toxicity are considered related to cediranib and do not resolve to grade 1 or below with maximum supportive care and following a dose interruption of up to 14 days (21 days in consultation with the CI), the next dose level of cediranib below that being dosed should be instituted
- If symptoms do not resolve, and it is considered medically appropriate, investigators may choose to permanently discontinue cediranib

For patients who have multiple low grade adverse events (for example, diarrhoea, weight loss, dehydration and fatigue) short dose interruptions (ie, 2 - 5 days) of cediranib tablets may help. Treatment can be restarted on resolution at the same dose.

Two dose reductions for the cediranib treatment will be permitted during the study. No re-escalation of dose is permitted.

A maximum of a 14-day (21-day in consultation with the CI) delay in dosing for cediranib is permitted. If a longer interruption is required due to unresolved toxicity, cediranib should be discontinued. In addition, there are certain circumstances in which study medication should be permanently discontinued (see [section 13.1](#)).

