## 7.4.2 Management of toxicity attributable to gefitinib

Dose interruptions should be used as the first approach to managing toxicity and dose reduction may be considered.

The events for which de-escalation of the gefitinib dose is recommended include:

- CTCAE grade 3 or higher toxicities of duration >3 days that are considered to be related to study treatment that are not responding to maximal supportive care within 48 hours, at the discretion of the investigator.

With the EXCEPTION of

- Rash ([section 7.4.2.1](#))
- Interstitial lung disease ([section 7.4.2.2](#))
- Diarrhoea ([section 7.4.3](#))

the following management plan should be followed for management of toxicity attributable to gefitinib:

Dose interruptions should be used as the first approach to managing toxicity. For CTC Grade 3 or more, dosing with gefitinib should be interrupted. Gefitinib dosing may be withheld for up to 14 days (or 21 days in consultation with the CI) for management of toxicity. If a longer interruption is required due to unresolved toxicity, gefitinib should be discontinued.

- If the symptoms promptly resolve to grade 1 or below with supportive care, consideration should be given to continuing the same dose of gefitinib along with appropriate continuing supportive care
- If the symptoms of the toxicity are considered related to gefitinib and do not resolve to grade 1 or below with maximum supportive care and following a dose interruption of up to 14 days (or 21 days in consultation with the CI), the next dose level of gefitinib below that being dosed should be instituted
- If the symptoms do not resolve and it is considered medically appropriate, investigators may choose to permanently discontinue gefitinib

For patients who have multiple low-grade adverse events short dose interruptions (ie, 2- 5 days) of the gefitinib tablets may help. Treatment can be restarted on resolution at the same dose

One dose reduction for the gefitinib treatment will be permitted during the study. No re-escalation of dose is permitted.

A maximum of a 14-day (21-day in consultation with the CI) delay in dosing for gefitinib is permitted. If a longer interruption is required due to unresolved toxicity, gefitinib should be discontinued. In addition, there are certain circumstances in which study medication should be permanently discontinued (see [section 13.1](#)).

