### k) Assessment dates during trial treatment

The cycle start assessment should be carried out on the day the patient begins the next cycle of study treatment. **Clinic assessments and MRI assessments will occur at the specified time points irrespective of trial treatment holidays.** E.g a 6 week cycle may only contain 3 or 4 weeks of trial treatment if a patient has had a trial treatment holiday during that cycle. If either treatment is delayed for more than 14 days due to toxicity (or 21 days if the CI has permitted a 21 day treatment holiday), the patient should cease taking the medication and continue with the cycles of the other study treatment. If both the study treatments are delayed for more than 14 days due to toxicity (or 21 days if the CI has permitted a 21 day treatment holiday), the discontinuation assessment should be performed and the patient withdrawn from the trial.

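### Sections 7.4.1 and 7.4.2 say both to stop the drug and to restart it one level lower when related toxicity is still grade 3 or more at the end of the permitted pause

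*Protocol*

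**What the plan says.** Protocol section 7.4.1 sets the general plan for cediranib toxicity, and four of its statements bear on toxicity that does not settle.

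- Interruption: "For CTC Grade 3 or more, dosing with cediranib should be interrupted".
- Limit on the interruption: "Cediranib dosing may be withheld for up to 14 days (21 days in consultation with the CI) for management of toxicity". The next sentence reads "If a longer interruption is required due to unresolved toxicity, cediranib should be discontinued", and the closing paragraph of the section repeats it.
- Second bullet: where symptoms attributed to the drug "do not resolve to grade 1 or below with maximum supportive care and following a dose interruption of up to 14 days" (or the longer period agreed with the Chief Investigator), the instruction is that "the next dose level of cediranib below that being dosed should be instituted".
- Third bullet: if symptoms do not resolve, permanent discontinuation is left to the investigator's choice.

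Section 7.4.2 has the same structure for gefitinib: "the next dose level of gefitinib below that being dosed should be instituted" stands beside "If a longer interruption is required due to unresolved toxicity, gefitinib should be discontinued", again with an optional stop in the third bullet.

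Three other sections deal with delays beyond 14 (21) days. Section 8.2(k) says that for a single delayed drug "the patient should cease taking the medication and continue with the cycles of the other study treatment". Section 7.1 says that such delays lead to withdrawal from the study. Section 13.1 lists grade 3 or higher toxicity with such a delay among the possible reasons for stopping treatment. Table 5 in section 7.3.4 gives the dose levels.

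**The concern.** A dose-modification rule should give one action for one clinical state. Here, for a state that the plan itself foresees, two obligatory instructions point in opposite directions and a third turns one of them into an option. The second bullet, which orders the lower dose, has no upper limit of grade.

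Patient safety is at stake first: one sentence, followed literally, re-doses a patient whose severe toxicity is continuing, while another permanently removes a study drug. Consistency between sites is at stake as well. Two sites could treat identical patients differently and both be compliant, so central monitoring would have no basis for calling either choice a deviation.

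**Working it through.** There is no arithmetic in the plan to reproduce. The check sets the rules side by side for one defined patient and then varies the grade and the dose.

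**Reference patient.** On cediranib 30 mg, with cediranib-related toxicity that is not among the exceptions listed in 7.4.1, still at grade 3 on the last permitted day of the pause despite maximum supportive care.

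1. *Interruption and limit sentences.* Grade 3 calls for interruption, and the toxicity is still grade 3. The permitted time is used up, so a longer interruption would be required because of unresolved toxicity. The instruction is to discontinue (should).
2. *Second bullet.* The toxicity has not settled to grade 1 or below after the permitted interruption, so the trigger is met. The instruction is the next lower level (should).
3. *Third bullet.* Symptoms have not resolved. Stopping is the investigator's choice (may). This fits neither obligation in step 1 nor that in step 2.

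**Vary the grade.**

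| State at end of pause | Interruption and limit sentences | Second bullet | Consistent? |
|---|---|---|---|
| Grade 1 or below | Not triggered | Not triggered | Yes |
| Grade 2 | Stop only if a longer pause is judged necessary | Next level down | Yes, by judgement; no criterion given |
| Grade 3 or more | Stop | Next level down | No |

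**Vary the dose (Table 5).**

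| Current dose | Second bullet gives | Other route gives |
|---|---|---|
| Cediranib 30 mg | 20 mg, (30 − 20)/30 = 33% lower | 0 mg |
| Cediranib 20 mg | 15 mg, (20 − 15)/20 = 25% lower | 0 mg |
| Cediranib 15 mg | Stop | Stop |
| Gefitinib/placebo 500 mg | 250 mg, (500 − 250)/500 = 50% lower | 0 mg |
| Gefitinib/placebo 250 mg | Stop | Stop |

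The two routes agree at the lowest level of each drug and disagree above it. Every patient starts above it.

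**Do other sections settle it?** Sections 7.1, 8.2(k) and 13.1 all point towards stopping, but each acts only once the delay exceeds 14 (21) days. A site that follows the second bullet restarts the drug when the permitted interruption ends, so the delay need never exceed the limit and those rules need not come into play. None of them qualifies the second bullet.

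**Which toxicities.** Section 7.4.1 excepts proteinuria, hypothyroidism, hypertension and RPLS; section 7.4.2 excepts rash, interstitial lung disease and diarrhoea. Section 7.4.1.1 nevertheless sends proteinuria of grade 3 or more back to 7.4.1.

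**The case against.** The strongest reply is that the triggers differ. The discontinuation sentence is conditional on needing a pause beyond the limit, whereas the second bullet concerns a pause within it. The three bullets can then be read as a ladder: same dose after prompt resolution, one level down without resolution, optional stop if that fails. Section 7.4 presents the guidance as recommended, and sections 7.1, 8.2(k) and 13.1 all lean towards stopping.

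This reply succeeds for residual grade 2, where the grade alone does not require interruption and the need for a longer pause can be a matter of judgement. It fails at grade 3 or more, because there the interruption rule is set by grade and itself makes a longer pause necessary. The ladder reading explains the third bullet but still has its second step re-dose a patient at grade 3.

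A reader might infer more than this, and the document does not support it:

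- *That de-escalation is due both at about 3 days and at 14 to 21 days.* The line on toxicity lasting more than 3 days without response in 48 hours is at the investigator's discretion, and the 14 days are a ceiling, not a waiting period.
- *That slow but complete resolution has no rule.* Sections 7.3.4 and 7.4 allow dose reduction in general terms, and the protocol does not define prompt resolution.
- *That this rule governs nearly all toxicity.* Diarrhoea, hypertension, fatigue, skin and thyroid effects, thrombocytopenia, and renal and hepatic impairment have guidance of their own, although the formal exceptions are fewer.
- *That the listed safety outcomes would be distorted.* Sections 2.6.3 and 16.5 list adverse events, vital signs, ECG, laboratory findings and examinations. Dose reductions and exposure are not among them, and the stopping guide in 16.5 counts treatment-related events of grade 3 or more.

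**Conclusion.** The contradiction is real and narrow. It applies to drug-related toxicity still at grade 3 or more at the end of the permitted pause, managed under the general plan, in patients on cediranib 30 or 20 mg or on gefitinib/placebo 500 mg. In that state the text requires both stopping and restarting one level lower, and also makes stopping optional.

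For a patient on full dose the difference is 20 mg against 0 mg of cediranib, or 250 mg against 0 mg of gefitinib/placebo. The protocol gives no figure from which to estimate how many patients would reach this state, so no frequency is claimed. The sample size and the method of the primary analysis do not depend on it.

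The conclusion rests on one reading: that the interruption rule for grade 3 or more continues to apply for as long as the toxicity stays at that grade. Nothing in 7.4.1 or 7.4.2 limits it to onset. Because the text can lead to re-dosing during ongoing severe toxicity, it should be corrected even if few patients are affected. Which instruction is right is a clinical decision, and no view on it is given here.

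**What to change.** Reconcile the second and third bullets of 7.4.1 and 7.4.2 with the interruption and 14/21-day sentences in the same sections, and with 7.1, 8.2(k) and 13.1. Toxicity unresolved at the end of the permitted pause should have exactly one instruction for each grade, worded the same for both drugs. The sponsor's clinicians decide which instruction stands. While these sections are open, state whether proteinuria of grade 3 or more follows the general plan, since 7.4.1 excepts it and 7.4.1.1 refers it back.

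The cost is an amendment that rewords two parallel sections and aligns the cross-references, plus notice to sites. It adds no visits, data items or patients.
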